## Abstract

**Background:**

Recent progress in the pathophysiology of heart failure (HF) has led to the development of new therapeutic options such as gene therapy and the use of adeno-associated viral (AAV) vectors. Despite the promising results in early clinical trials of gene therapy for HF, various obstacles have been faced, such as the presence of neutralizing antibodies (NAbs) against the capsid vectors. NAb activity limits vector transduction levels and therefore diminishes the final therapeutic response. Recent studies evaluating the prevalence of NAbs in various populations found considerable geographic variability for each AAV serotype. However, the levels of NAbs in Latin American populations are unknown, becoming a limiting factor to conducting AAV vector therapeutic trials in this population.

**Objective:**

The goal of this study is to determine for the first time, the prevalence of anti-AAV NAbs for the serotypes 1, 2, and 9 in HF patients from the city of Bucaramanga, Colombia, using the *in vitro* transduction inhibition assay.

**Methods:**

We will conduct a cross-sectional study with patients who periodically attend the HF clinic of the Cardiovascular Foundation of Colombia and healthy volunteers matched for age and sex. For all participants, we will evaluate the NAb levels against serotypes AAV1, AAV2, and AAV9. We will determine NAb levels using the *in vitro* transduction inhibition assay. In addition, participants will answer a survey to evaluate their epidemiological and socioeconomic variables. Participation in the study will be voluntary and all participants will sign an informed consent document before any intervention.

**Results:**

The project is in the first phase: elaboration of case report forms and the informed consent form, and design of the recruitment strategy. Patient recruitment is expected to begin in the spring of 2016. We expect to have preliminary results, including the titer of the viral vectors, multiplicity of infections that we will use for each serotype, and the general validation of the assay, at the end of 2016. The final results are expected mid-2017.

**Conclusions:**

This project is the first effort to evaluate NAb levels against AAV1, AAV2, and AAV9 serotypes in patients with HF in Latin America. Our results will allow us to check the cross-reactivity response between the serotypes assessed, to describe the epidemiological characteristics of the participant population, and to set up a link with earlier reports of NAb prevalence in the literature.

## Introduction

Heart failure (HF) is the cardiovascular disease (CVD) with the highest mortality and morbidity globally. Recent reports indicate that up to 1% to 2% of adult populations in developed countries have HF, with an increasing prevalence of ≥10% among people ≥70 years old [1]. Despite the significant improvement in management of disease symptoms and the decreased disease progression achieved with newly developed pharmacological therapies and invasive procedures, alternative therapeutic approaches are still urgently needed to provide a definitive cure [2]. Recent advances in structural and molecular cardiology have shown that abnormalities in the calcium cycling proteins play a significant role in the induction and progression of HF. Decreased sarcoplasmic reticulum Ca^2+^-ATPase (SERCA2a) activity has been described to be a critical pathway responsible for pathologic modification of the cardiomyocytes during HF [3]. These findings, together with advances in gene transfer technologies, have led to gene therapy being considered as a new therapeutic option for CVDs, and specially for HF. Encouraging results from early clinical trials involving the use of adeno-associated viral (AAV) vectors delivering the *SERCA2* gene have generated high expectations [4]. Additionally, other proteins have shown promising results in preclinical models of HF, such as S100A1 and adenylyl cyclase 6 [5,6].

### Emergence of Gene Therapy as a Therapeutic Option for HF and CVD

Three elements must be considered in the design of a gene therapy strategy: the therapeutic gene that will be cloned into the transgene expression cassette; the target cells or tissues in which the vector will deliver the genetic material; and the viral vector used to facilitate entry of the gene into the target tissue [7]. Viral vectors consist of genetic material surrounded by a protein capsid, which facilitates the transcellular transport and internalization of the therapeutic gene into the target cell [7]. Additionally, the capsid protects the transgene expression cassette from lysosomal degradation during its trafficking to the nucleus [8]. The discovery of viral vectors with cardiomyocyte and endothelial tropism accelerated the progression of gene therapy as a therapeutic option for HF [9]. Novel transductional modifications of the first-generation vectors and translational strategies in the transgene expression cassettes have been developed to achieve higher and longer-term expression of the transfected gene while trying to decrease the amount of adverse effects [10]. As Mingozzi and High state, “The gene is the active agent of therapeutic, but the vector, in most cases derived from a virus, is also a critical determinant of therapeutic success and of the toxicity profile” [11]. Importantly, depending on the viral vector selected, the immune response to the vector or to the cells expressing the modified gene varies and can become a limiting factor for successful therapy [12]. Specific immune responses can prevent vector gene transfer after readministration of the vector, limit the duration of gene expression, or produce an immune response against the genetically modified cells [13].

Viral vectors derived from adenovirus, retrovirus, lentivirus, or AAV have been used as therapeutic tools for a broad spectrum of genetic and nongenetic diseases, including CVD and HF. Lentivirus vectors originate from human immunodeficiency virus 1 and have been used successfully to treat hematopoietic monogenic diseases thanks to their therapeutic long-term effects [14,15]. However, their use in gene therapy applications for CVD or specifically for HF is more limited, given their relatively poor transduction after systemic administration and the risk of insertional mutagenesis [16]. Adenoviral vectors are non-enveloped double-stranded DNA vectors, which are not able to insert the genome into the host cell DNA. Adenovirus serotype 5 has been used predominantly in preclinical and clinical trials of gene therapy for myocardial infarction and ischemic diseases, in which short-term transgenic expression is required [17].

The most commonly used viral vectors for HF and the focus of our project are the AAV vectors. AAV vectors are single-stranded DNA vectors with a favorable safety profile and the ability to achieve long-term transgene expression in a wide range of tissues, including heart [18]. The storage capacity of the AAV vector (up to 4.7 kB) restricts the size of the transgene expression cassette that can be used and needs to be considered beforehand [19]. More than 100 AAV serotypes existing in nature have been reported, many of them with variable tissue tropism, which is determined by the structure of the proteins in the capsid [18]. AAV1, AAV6, AAV8, and AAV9 have been reported as the serotypes with favorable tropism for cardiomyocytes after systemic administration. However, tropism for other cell types, such as hepatocytes, is still present and needs to be carefully considered before any clinical trial [9,20,21]. Satisfactory preclinical results in large experimental animal models with a heart anatomy similar to that of humans led to the clinical translation of AAV-based technology for transgene expression of key proteins involved in the progression of HF, such as SERCA2a [22]. The first clinical trial for HF was conducted using an AAV1 vector, the Calcium Upregulation by Percutaneous Administration of Gene Therapy in Cardiac Disease (CUPID) trial [23]. Simultaneously, two other clinical trials are in the late phases of recruitment, the phase 2 study Investigation of Safety and Feasibility of AAV1/SERCA2a Gene Transfer in Patients With Chronic Heart Failure (SERCA-LVAD; NCT00534703) and the AAV1-CMV-SERCA2a Gene Therapy Trial in Heart Failure (AGENT-HF; NCT01966887), with results expected in 2016.

### Immune Response Against AAV Vectors

Immune responses of T cells against antigens of the AAV capsid presented in association with major histocompatibility complex class I on the surface of transduced target cells can reduce long-term gene expression, after an immune rejection of the genetically modified target cells [11]. Transient immunosuppressive therapies or AAV capsid variants that reduced the presentation of peptides derived from the AAV capsid can decrease this risk of immune responses [24,25]. The vector capsid is, in most cases, an exact replica of the viral capsid, and thus the immune response against the vector may be influenced by previous exposure of the immune system to environmental viruses from which the vector is designed [26]. Humans, early in life, are naturally exposed to wild-type AAV, and consequently the frequency of seropositivity of anti-AAV steadily increases after 2 years of age [26]. Humoral immunity to AAV can also be found in infants, as a result of vertical transmission of anti-AAV antibodies from the mother. In adults, anti-AAV2 antibodies are the most prevalent (up to 70% of healthy humans), followed by serotypes such as AAV5, AAV9, and AAV8, which are much less frequent [27]. Although the risk of inflammatory immune responses after AAV vector transduction is significantly lower than with adenoviral vectors, there are still significant immunological complications that must be evaluated. In particular, the high prevalence of preexisting anti-AAV neutralizing antibodies (NAbs) in the population may result in rapid neutralization of vectors derived from AAV, preventing adequate gene transfer [12]. Similarly, the induction of NAbs after AAV-based gene therapy impedes adequate therapeutic response following readministration of AAV vectors [7,28].

### Anti-AAV NAbs

There is a high degree of amino acid sequence conservation between AAV capsids, leading to anti-AAV antibody cross-reactivity in a wide range of serotypes [29]. Although antibodies to AAV2 are clearly the most prevalent in humans (up to 70%), the natural host for this serotype, antibodies that recognize virtually all serotypes of AAV may be found in a high proportion of humans [26]. Studies have shown that, after AAV vectors were introduced into the systemic circulation in humans, the preexisting humoral immunity to AAV vectors profoundly reduced transduction efficiency in the target tissue. Results of the first clinical trial for hemophilia B showed that relatively low titers of NAbs, as low as 1:17, can completely neutralize large vector doses, without detection of transgene expression [12]. The existence of anti-AAV NAbs is one of the main limitations faced in gene therapy clinical trials after intravascular delivery of AAV vectors. In the CUPID 2 trial, patients with high levels of NAbs were excluded. Of the 509 patients initially evaluated, >50% were excluded for presenting levels of NAbs outside of the safety range established in the study [30], suggesting the importance of prior determination of anti-AAV NAb circulating levels in different populations.

The prevalence of NAbs against AAV in humans was initially reported in the 1960s and 1970s, mainly anti-AAV1 and -AAV2 serotypes, the only known serotypes at that time. NAb variation is estimated at between 30% and 80% based on previously published studies in other populations [31,32]. More recent studies have evaluated the prevalence of NAbs in the most commonly used serotypes for preclinical studies (AAV5, AAV7, AAV8, and AAV9) and compared them with previously described serotypes. One study that collected samples from 10 countries on 4 continents (United States, Europe, Africa, and Australia) showed a prevalence of NAbs to AAV2 of between 30% and 60% of the total population [27]. This was significantly higher than the prevalences of NAbs to AAV7, AAV8, and AAV9 serotypes, which were reported to be between 15% and 30%. Notably, higher frequencies of NAbs were observed for all AAV serotypes in Africa than in the other regions [27]. However, none of the existing reported studies have included a Latin American population.

An interesting finding is the significant variability in the prevalence of anti-AAV NAbs, influenced by the geographic origin of the population. While the prevalence of NAbs against AAV1 in Africa and China is around 50% to 70%, in other countries such as Belgium, Greece, Italy, and the United States, it is only 20% to 30% [27]. Overall, the prevalence of anti-AAV NAbs appears to be greater in developing countries. Factors such as living conditions, population density, hygienic conditions, different levels of health care, and the AAV detection method for NAbs can influence these results; in particular, the prevalence of anti-AAV1 NAbs was higher in women than in men [27]. The health status of the target population can also affect the prevalence NAbs against AAV, especially in those patients with a compromised immune system. These people had a lower prevalence of anti-AAV NAbs than that in the healthy population [26,27,33,34]; furthermore, the prevalence of NAbs was higher in elderly than in younger populations [35].

### AAV Antibody Determination

Diverse methods have been developed to detect antibodies against different serotypes of AAV. Some of them are based on total binding antibodies to the AAV capsid, and others on the functional determination of antibodies that neutralize AAV vector transduction *in vitro* or *in vivo* [29]. The first reports, in the 1970s, were based on binding of antibodies to AAV capsid vector evaluated by enzyme-linked immunosorbent assay (ELISA) and Western blot [32]. These studies focused on AAV1 and AAV2. The discovery in the last decade of new AAV vectors required more accurate assays to evaluate not only the level of binding but also the effect of the specific NAb for each AAV serotype on vector activity. Given the profound effect of anti-AAV antibody on transduction efficiency, the development of sensitive and reliable methods for measuring patients’ titers of NAbs is critical before starting a clinical trial with gene therapy. Furthermore, the method of choice must ensure correlation of titers with the clinical outcome reported for gene therapy.

#### Elisa

ELISA is based on a capture assay in which the entire AAV capsid or peptides coated on a plate and AAV immunoglobulin antibodies present in serum are detected with a secondary antibody. ELISAs are easier to configure and are relatively sensitive at determining antibody levels. However, the total amount of anti-AAV antibodies is not always proportional to its neutralizing activity, especially in people with low titers, making this assay unreliable for determining the eligibility of people for their participation in clinical trials with AAV vectors.

#### In Vitro Cell-Based Assays

These are among the most widely used methods to determine anti-AAV NAbs [27,36,37]. Specifically, the *in vitro* transduction inhibition assay has become the standard test to evaluate the presence of anti-AAV NAbs [37]. Typically, an AAV vector expressing a reporter gene is mixed with serially diluted amounts of the test sample, and this vector serum mixture is incubated with the cell line of choice, which is then analyzed for reporter gene expression. The starting dilution of the test sample, which defines assay sensitivity, varies across studies, ranging from 1:2 to 1:20. The NAb50 titer is reported as the highest serum dilution that inhibits the transduction of the reporter gene by 50% [37]. While NAb *in vitro* assays are relatively easy to set up and give consistent results, they have some limitations: the most important derives from the fact that most of the AAV serotypes are highly inefficient for *in vitro* cell transduction. This limitation can be at least partially overcome with the use of reporter genes with high detection sensitivity (eg, luciferase) and cell lines more permissive for AAV transduction [37]. In addition, several related parameters of the cell culture conditions can contribute to variability of the assay, such as the cell line used, cell density, and the number of passages of cells during cultivation.

In summary, recent reports highlight the importance of identifying the prevalence of NAbs for each AAV serotype in various human populations, due to the serotypes’ geographic variability and their major role in selection of participants for AAV vector clinical trials. This increases the importance of conducting NAb prevalence studies in the Latin American population. Considering the major impact of CVD on the health care systems of developing countries, we intend to determine the prevalence of anti-AAV vector NAbs for the serotypes AAV1, AAV2, and AAV9 in patients with HF in the Cardiovascular Foundation of Colombia (FCV) by the *in vitro* transduction inhibition assay.

## Methods

We will conduct a cross-sectional study to evaluate NAbs against AAV1, AAV2, and AAV9 serotypes in patients with HF at the FCV-HF clinic. Patients who fulfill the inclusion criteria will be invited to participate in the study. Those who accept will be asked to read and ask the questions they deem relevant to informed consent before signing the form (see Multimedia Appendix 1). Once the patients consent to participate, a standardized and approved survey to evaluate epidemiologic and socioeconomic variables and major CVD risk factors will be applied and complemented with relevant clinical information obtained from the electronic medical record system (SAHI 2.0 software, integrated hospital management system) developed by the FCV. A physical examination will be performed, including evaluation of blood pressure levels, anthropometric measurements, and a record of the last echocardiographic parameters available. Finally, a sample of peripheral blood will be collected from each participant to determine the presence of anti-AAV NAbs.

### Study Population

We will evaluate 60 patients with a diagnosis of HF (American Heart Association stage B or higher criteria) followed in the FCV-HF clinic (see Textbox 1 for inclusion criteria for the patient group). All adult patients (≥18 years old) followed in the HF clinic at FCV will be eligible for the study. We will use various methods to recruit patients, including electronic clinical data from the SAHI 2.0 records. Additionally, we will invite 60 healthy volunteers, matched by age and sex, to participate. Participants will be considered as healthy volunteers if they are ≥18 years old, nationals from a Latin America country with a residence address in Colombia, and not meeting any of the exclusion criteria detailed in Textbox 2. We selected the number of participants as convenience size due to the internal financial and technical limitations of the project.

Inclusion criteria for patients in the ANVIAS study.Age ≥18 yearsDiagnosis of heart failure stage B or higher according to the American Heart Association criteriaNational of a Latin America country with residence address in ColombiaFollowed in the Cardiovascular Foundation of Colombia heart failure clinic

Exclusion criteria for patients simultaneously presenting with heart failure and for volunteer participants the ANVIAS study.Multiple blood transfusionsRecent plasmapheresisInfection with human immunodeficiency virusImmunosuppression or recent treatment with corticosteroidsSolid organ or bone marrow transplantationDiagnosis of Chagas diseasePregnancyPreexisting condition of asthma, obstructive sleep apnea, or chronic obstructive pulmonary diseasePrior hormone replacement therapyHeavy drinking, defined as the consumption of ≥5 alcoholic drinks on the same occasion on each of ≥5 days in the past 30 days (US Substance Abuse and Mental Health Services Administration definition)

### Storage of Biological Material

Participants will be asked to consent to donate biological material to be stored according to all quality and ethical requirements in the biobank of the FCV. The FCV biobank is a biomedical platform for future research, which is of great relevance in contributing to establishing bridges between basic, translational, and clinical research, and health care practice. Importantly, participants in this proposed study will be required to grant additional consent for taking and storing samples in the biobank (see Multimedia Appendix 1).

### Blood Sample Collection and Separation of Components

Samples of peripheral blood will be collected by antecubital venipuncture with a Vacutainer system (Becton, Dickinson and Company, Franklin Lakes, NJ, USA) into 2 tubes containing 4 mL of EDTA anticoagulant and labelled to identify the participant. Then, the sample will be centrifuged to separate the components and stored according to established protocols by the FCV biobank. A physical and digital date and time record of sampling separation and storage components will be kept, as well as the name of the person responsible for the procedures.

Samples will be handled from the first to the final phase by the following FCV biobank storage steps: 1) obtaining informed consent for storage of samples in the biobank: Protocol PR-BIO-01, 2) blood sampling: Protocol PR-BIO-03, 3) transporting biological samples: Protocol PR-BIO-02, 4) receiving and storing samples: Protocol PR-BIO-05, 5) quality control of human biological material, storage, and registration: Protocol PR-BIO-08.

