#### Day 2: Sample Controls and AAV Vector Preparation

For transduction, we will prepare serial dilutions of 10 mL of patient serum and a control sample using fetal bovine serum as the diluent (Table 1). One control sample will correspond to 100% transduction of the vector and another to 0% transduction of the vector to allow for determining the background luminescence signal. The viral vector will be diluted to the concentration selected (according to the desired working MOI) in DMEM without the use of fetal bovine serum. Subsequently, we will add 20 μL of the vector to each of the sample dilutions and controls. These samples will be grown for 1 hour at 37°C and, subsequently, 7.5 μL of each neutralized sample will be added to the cell culture medium. Cells will remain in overnight incubation at 37°C and 5% CO_2_.

**Table 1 table1:** Example^a^ of half-log dilution preparation for the test sample and control using fetal bovine serum as the diluent before being mixed with the viral vector (20 μL) and added to 96-well plated cultured cells.

Dilution no.	Relation	Volume (μL) of sample/control	Volume (μL) of diluent
1	1:1	40	0
2	1:3.16	12 of dilution 1	26
3	1:10	12 of dilution 2	26	
4	1:31.6	12 of dilution 3	26
5	1:100	12 of dilution 4	26
6	1:316	12 of dilution 5	26
7	1:1000	12 of dilution 6	26
8	1:3160	12 of dilution 7	26

^a^Modified from Meliani et al [37].

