## Results

We have completed the first phase of the project. During this stage, all the documents necessary for recording and storing information have been elaborated and submitted to the ethical committee of the FCV for approval. We expect to begin recruiting patients in the spring of 2016. We expect to complete the second phase, in which we will validate all the protocols for the project—including determining the titer of the viral vectors, selecting the MOI that we will use for each serotype, and validating the assay—by the end of 2016. Finally, we will conduct the third phase, in which we will analyze serum samples from patients and healthy volunteers, during 2017. We expect to have the first results in mid-2017.

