## Discussion

For this project, we will evaluate anti-AAV1, -AAV2, and -AAV9 NAbs by using the *in vitro* transduction inhibition assay, to determine the presence, activity, and titers of NAbs in patient sera. Several critical steps and validation of the protocol should precede analysis of the patient samples (eg, selection of MOI, selection of the cells to be used during the assay). We expect that the final results may indicate the seroprevalence of NAbs for the selected serotypes and allow for comparison with previously reported results from other populations. The causes of the demonstrated high variability between the evaluated populations continue to be debated, and more studies including different healthy populations and under specific pathologic circumstances need to be conducted worldwide. Importantly, the method of determination should be standardized to obtain more reliable and comparable data. Recent reports support the higher sensitivity of intramuscular *in vivo* assays to determine NAb response [42], suggesting that *in vivo* NAb assays are more sensitive than *in vitro* assays for determining inclusion and exclusion criteria in clinical trials; however, the technical difficulties and higher cost associated with using *in vivo* assays in population studies mean that *in vitro* assays still have an important function.

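### Blood is drawn only into EDTA tubes, which give plasma, but the assay is specified for serum; the Day 2 volumes also do not reconcile

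*Protocol article*

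**What the plan says.** **Collection.** Under Blood Sample Collection and Separation of Components, venous blood goes "into 2 tubes containing 4 mL of EDTA anticoagulant and labelled to identify the participant" and is then centrifuged. No other tube is named. The same section refers to biobank procedures that are not shown, among them "blood sampling: Protocol PR-BIO-03".

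**Assay.** Day 2 states: "we will prepare serial dilutions of 10 mL of patient serum and a control sample using fetal bovine serum as the diluent". Results says "we will analyze serum samples from patients and healthy volunteers", and Discussion speaks of "titers of NAbs in patient sera".

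**Volumes.** Table 1, labelled an example, starts with 40 μL of sample. Each later tube receives 12 μL from the tube before it plus 26 μL of diluent; the last entry is "12 of dilution 7", with no removal listed after it. Day 2 continues: "we will add 20 μL of the vector to each of the sample dilutions and controls". After one hour, 7.5 μL of each mixture goes onto the cells.

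**Reading.** Day 4 expresses each luciferase signal as a percentage of one maximum signal, after subtracting background, and bases the titer on inhibition of at least 50%. Day 2 names a 100% transduction control but gives neither its volume nor its matrix, apart from fetal bovine serum as diluent.

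**The concern.** Two things do not fit together.

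First, EDTA blood yields plasma, so the stated collection cannot supply the serum that the stated assay needs. The tube is fixed at recruitment (expected from spring 2016), while validation is to finish at the end of 2016 and samples are to be analysed in 2017. If validation shows that plasma behaves differently, the tubes already drawn cannot be turned into serum.

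Second, inhibition is a ratio to a common maximum signal. That ratio reflects antibody alone only if test and reference wells agree in matrix and vector dose. The stated volumes do not give equal vector doses across the dilution series.

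At stake are the absolute prevalence, which is the study's objective, its comparison with other populations, and the titers at the top of the range.

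**Working it through.** **Dilution ratios (Table 1).** Step factor = (12 + 26)/12 = 3.167. Its successive powers are 3.17, 10.03, 31.8, 100.6, 318, 1008 and 3193, against the stated 3.16, 10, 31.6, 100, 316, 1000 and 3160. The largest deviation is 1.05%, so the ratios are right.

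**Starting volume.** I read the collection sentence as two 4 mL tubes, so 2 × 4 = 8 mL of whole blood. Assuming a plasma yield of 45–60%, that gives 3.6–4.8 mL. The stated 10 mL exceeds even the whole blood drawn, and 10,000/40 = 250 times the Table 1 volume.

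**Vector per well.** Volume left before vector:

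- tube 1: 40 − 12 = 28 μL
- tubes 2–7: 12 + 26 − 12 = 26 μL
- tube 8: 12 + 26 = 38 μL

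Vector in the 7.5 μL plated = 7.5 × 20/(volume left + 20):

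- tube 1: 150/48 = 3.13 μL
- tubes 2–7: 150/46 = 3.26 μL
- tube 8: 150/58 = 2.59 μL

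Tube 8 against tubes 2–7: 1 − 46/58 = 20.7% less.

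**Apparent inhibition from dose alone.** Assume the signal is proportional to vector dose. Apparent inhibition = 1 − (control volume + 20)/(tube volume + 20). The control volume is not stated, so I vary it:

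| Control volume before vector | Tube 1 | Tubes 2–7 | Tube 8 |
|---|---|---|---|
| 10 μL | 37.5% | 34.8% | 48.3% |
| 20 μL | 16.7% | 13.0% | 31.0% |
| 26 μL | 4.2% | 0% | 20.7% |
| 28 μL | 0% | −4.3% | 17.2% |
| 38 μL | −20.8% | −26.1% | 0% |
| 40 μL | −25.0% | −30.4% | −3.4% |

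No entry reaches 50%, and the sign changes with the control. With a 26 μL control, tube 8 is called at a true inhibition of 1 − 0.5/0.793 = 37% instead of 50%.

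**Where a matrix effect would sit.** Participant material in the well, taking 100 μL of medium plus 7.5 μL of mixture:

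- 1:1: 7.5 × 28/48/107.5 = 4.1%
- 1:3.16: 7.5 × 26/46/3.167/107.5 = 1.2%
- 1:10: 7.5 × 26/46/10.03/107.5 = 0.4%

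Any EDTA or plasma effect is therefore concentrated in the first one or two dilutions.

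**Illustration only.** If a share x of true negatives were misread, apparent prevalence = p + (1 − p)x. With p = 30% and x = 0–10% (both assumed), it is 30–37%. The 95% half-width at n = 60 is 1.96 × √(0.3 × 0.7/60) = 11.6 points.

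**The case against.** A reader might infer that matrix and dose effects will be counted as neutralization and so inflate the prevalence. The documents do not support that, for these reasons:

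- They give no effect of EDTA or plasma on cells, luciferase or titer. The sample is undiluted only before vector is added; in the culture well it is about 4% by volume.
- A control unmatched in matrix or volume is inferred, not stated. The article gives main features only and refers to a published protocol for the rest, so the missing control detail is not in itself an error.
- The dose imbalance is largest at 1:3160. A sample near the threshold there would ordinarily already be positive at lower dilutions, so its titer may move one half-log step while its status stays the same.
- Table 1 is an example and does not say whether 12 μL is discarded from tube 8. If the 10 mL was meant as a 10 μL aliquot of every dilution, each mix would be 30 μL and the imbalance would vanish; the text does not say so.
- The 10 mL looks like a unit slip. Day 1 has an equally implausible 10 mL for an additive in a 96-well format.
- Assay Validation plans cut point, specificity and selectivity work, which could detect a matrix effect.
- Patients and volunteers share the described matrix, so no differential bias between groups is shown.

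All of this limits the size of the harm. It does not remove the contradiction. The unseen biobank procedure might add a serum tube, but the article itself states the tube type and number and then names a different specimen in three places. Validation could reveal a plasma effect but could not convert tubes already drawn. Assay Validation also lets that work run alongside the project, whereas Discussion says it should come before sample analysis.

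**Conclusion.** The point holds as an inconsistency that should be settled before the first blood draw.

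- **Specimen.** EDTA plasma is collected and serum is specified. This may bias absolute prevalence and comparison with earlier reports. The size and direction cannot be derived from the documents. That the lowest dilutions decide status assumes that a sample counts as positive on inhibition of at least 50% at any dilution; the final cut point is left to validation.
- **Starting volume.** The 10 mL is impossible from about 8 mL of blood and conflicts with 40 μL. It is probably a unit slip, although 10 μL would not match Table 1 either.
- **Vector dose.** Followed literally, the 1:3160 well receives about 21% less vector than wells 2–7. The effect on measured inhibition assumes a linear signal, and its direction depends on the unstated control volume. It can shift the highest titers and hardly affects prevalence.

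Inflated prevalence is not demonstrated.

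**What to change.** Before recruitment:

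1. **Specimen.** Either add or substitute a serum tube and assay serum; or keep EDTA plasma, call it plasma in Day 2, Results and Discussion, and prepare the 100% transduction control in the same matrix and volume as the test wells. The first costs one tube type and no added visit. The second needs plasma free of neutralizing antibodies to all three serotypes, which is hard to source: the Introduction puts AAV2 antibodies at up to 70% in humans, and screening donors needs the assay itself.
2. **Starting volume.** Correct the 10 mL to the Table 1 volume; if an aliquot of each dilution was meant, say so.
3. **Vector dose.** Bring every dilution and control to one volume before adding the 20 μL of vector; for example, discard 12 μL from tube 8 and take 26 μL from each tube and control. Every mix is then 46 μL, each well gets 3.26 μL of vector, and dose-only apparent inhibition is 0% throughout. The cost is one pipetting step and a sentence in Day 2.
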